# Customized Human Milk Fortification Based on Measured Human Milk Composition to Improve the Quality of Growth in Very Preterm Infants: A Mixed-Cohort Study Protocol

**DOI:** 10.3390/ijerph18020823

**Published:** 2021-01-19

**Keywords:** body composition, growth, human milk fortification, preterm infants, standard fortification, target fortification

## Abstract

Adequate nutrition of very preterm infants comprises fortification of human milk (HM), which helps to improve their nutrition and health. Standard HM fortification involves a fixed dose of a multi-nutrient HM fortifier, regardless of the composition of HM. This fortification method requires regular measurements of HM composition and has been suggested to be a more accurate fortification method. This observational study protocol is designed to assess whether the target HM fortification method (contemporary cohort) improves the energy and macronutrient intakes and the quality of growth of very preterm infants, compared with the previously used standard HM fortification (historical cohorts). In the contemporary cohort, a HM multi-nutrient fortifier and modular supplements of protein and fat are used for HM fortification, and the enteral nutrition recommendations of the European Society for Paediatric Gastroenterology Hepatology and Nutrition for preterm infants will be considered. For both cohorts, the composition of HM is assessed using the Miris Human Milk analyzer (Uppsala, Sweden). The quality of growth will be assessed by in-hospital weight, length, and head circumference growth velocities and a single measurement of adiposity (fat mass percentage and fat mass index) performed just after discharge, using the air displacement plethysmography method (Pea Pod, Cosmed, Italy). ClinicalTrials.gov registration number: NCT04400396.

## 1. Introduction

### 1.1. Biological Advantages of Human Milk

Human milk (HM) is the first choice for feeding preterm infants [1], as it is the better option that compensates for the immature immune [2,3], vascular [4], and neurological [5] systems. In very and extremely preterm infants, HM has beneficial effects on the neurodevelopmental outcome [6] and preventive effects on morbidities, including retinopathy of prematurity [7], bronchopulmonary dysplasia [8], necrotizing enterocolitis [7,9], and late sepsis [9].

From a nutritional point of view, HM does not fulfill the needs of growing preterm infants, resulting in accumulated nutrient deficits, which may lead to extrauterine growth restriction and poor neurodevelopmental outcomes [10,11]. This is particularly true for protein deficits [12]. Early postnatal growth restriction, in turn, predisposes individuals to late metabolic diseases [11]. To prevent nutritional insufficiencies related to HM while taking advantage of its biological properties, HM multi-nutrient fortifiers are used for preterm infants [13,14,15].

### 1.2. Methods for Fortification of Human Milk

Human milk is fortified using the standard method, which consists of the addition of a fixed dose of a HM multi-nutrient fortifier, according to the manufacturer’s instructions [14]. This method does not take into account the great variability of the nutritional composition of HM [13,14,15,16] and so does not avoid the risks associated with energy–protein malnutrition, poor neurodevelopmental outcome, and metabolic bone disease [17,18,19]. In an attempt to overcome this problem, alternative individualized HM fortification methods have been proposed, particularly target fortification [15].

The target fortification method is based on the regular measurements of the energy and macronutrient contents of HM, in order to customize the target energy and macronutrients to each infant [20]. In addition to the multi-nutrient fortifier, modular protein, carbohydrate, and fat supplements may be added to HM to achieve the desirable nutrient targets for preterm infants [15,21,22].

### 1.3. Questions to Be Answered

Many authors [21,22,23,24] consider the target HM fortification to be a more accurate method to achieve adequate nutrition in preterm infants according to energy and protein intakes recommended by the European Society for Paediatric Gastroenterology Hepatology and Nutrition (ESPGHAN) [25]. However, this opinion is not unanimous, as other authors found that the target HM fortification method, as compared to the standard HM fortification, did not meet the recommended protein intake [26] or result in better growth outcomes [27]. The target fortification method has also been described as inconvenient, as a result of requiring a HM analyzer and being time-consuming and labor-intensive [27].

In order to comply with the ESPGHAN enteral nutrition recommendations for preterm infants in clinical practice [25], more studies which take into account the osmolality of feeds, feeding tolerance, and risk of necrotizing enterocolitis are needed [27], in order to determine the safe maximum concentrations of multi-nutrient fortifiers and modular protein supplements in the prescribed fluid intakes.

The current literature indicates that extremely and very preterm infants at term-equivalent age have a lower fat-free mass (FFM) and a greater fat mass percentage (FM%), compared with term-equivalent-age infants [28,29]. Reference values for body composition have been described for preterm infants [30,31], but the optimal body composition evolution in those infants remains to be determined. This lack of knowledge relates not only to the difficulty in defining the optimal nutrition intervention in preterm infants, a major factor determining body composition, but also to the current unavailability of a non-invasive, accurate, and easy to perform method for measuring body composition in fragile preterm infants under intensive care, including soon after birth [32,33].

### 1.4. A Contribution to Answer Some Unsolved Questions

In a cohort study of very preterm infants fed standard fortified HM, we previously evaluated the association between energy and macronutrient intakes and both weight gain velocity and body composition [34,35]. We concluded that the actual energy, protein, and fat intakes based on measured HM composition were significantly lower than the assumed intakes based on estimates of HM composition [34]. This nutritional strategy is associated with a suboptimal weight gain velocity and low adiposity [35]. From this evidence, following the ESPGHAN enteral nutrition recommendations for preterm infants [25], a nutritional strategy towards HM fortification based on measured HM composition was recently introduced in our unit. It is considered important to assess the effects of the newly implemented nutritional strategy.

### 1.5. Objective

The aim of this study protocol is to assess whether the newly implemented target HM fortification method, based on measured HM composition, improves both the energy and macronutrient intakes and the quality of growth in very preterm infants, compared with standard HM fortification.

### 1.6. Hypotheses

In very preterm infants, the customized HM fortification based on measured HM composition is expected to improve energy and macronutrient intakes, compared with the standard HM fortification. As a consequence of better nutrition provided by the target HM fortification, the quality of growth will improve, reflected by faster growth rates while achieving an adiposity at term-equivalent age similar to that of infants born at term.

## 2. Methods

### 2.1. Study Design

This single-center, observational mixed-cohort, effectiveness study in very preterm infants (<33 weeks of gestation) will compare the energy and macronutrient intakes and the growth and body composition between infants fed either target fortified HM, based on measured HM composition (the contemporary cohort), or standard fortified HM (the historical cohort).

### 2.2. Primary Outcome

We hypothesize that the HM fortification method based on measured HM composition will result in higher energy and macronutrient intakes and faster weight gain velocity than previously observed [35]. Weight gain velocity was chosen as the primary outcome to estimate the sample size because it is considered an important measure of preterm infants’ health [10,36].

### 2.3. Secondary Outcomes

In addition, we hypothesize that in infants fed target fortified HM, adequate linear and head growth velocities will be achieved [37,38], and adiposity at term-equivalent age will be more similar to that of term-equivalent-age infants [28,29].

### 2.4. Setting, Participants, Study Periods, and Variables

The study will be conducted at the Centro Hospitalar Universitário de Lisboa Central, in the Neonatology Unit and Human Milk Bank at Maternidade [name] da Costa, and the Nutrition Laboratory at Hospital Dona Estefânia.

Recruitment for the contemporary cohort of infants fed target fortified HM was estimated to start in February 2020, with a scheduled recruitment period of 16 months. We planned to compare it with a historical cohort fed standard fortified HM in 2014–2015 [34,35], as stated in the ClinicalTrials.gov NCT04400396 registry. However, there was a shortage in modular protein supplement from February to July 2020, precluding the adoption of the new nutritional protocol using the target HM fortification. In this context, the standard fortified HM arm will include infants from two cohorts: the historical study period (1 February 2014 to 28 February 2015) [33,34] plus the contemporary period from 1 February to 13 July 2020, during which the standard HM fortification was used.

The recruitment for the second contemporary cohort, including infants fed target fortified HM based on measured HM composition, effectively started on 14 July 2020 (Table 1).

The eligibility criteria are those followed by the historical cohort study [34,35], i.e., consecutive cases of newborns delivered <33 weeks of gestation, admitted to the NICU of Maternidade [name] da Costa (inborns and outborns), singletons or twins (=2), and exclusively HM-fed or predominantly (≥87.5% volume per day) HM-fed were eligible. Infants with a diagnosis of innate error of metabolism, those fed for two or more consecutive days with formula ≥12.5% of daily volume intake, and those transferred to other hospitals, deceased, or unavailable for body composition analysis after discharge will be excluded (Figure 1).

The study sample size was calculated based on the results obtained by Macedo et al. [35] with the present historical cohort (mean 10.1, SD 3.8 g/Kg/d) and those obtained by McLeod et al. [27] on a similar sample of very preterm infants fed a target HM fortification (mean 12.1, SD 1.6 g/Kg/d). Therefore, the sample was estimated to detect a difference of 2 g/kg/day in weight gain velocity, with a significance level of 0.05 and 80% power; thus, we estimated a required sample of 68 infants: 34 infants in each cohort.

### 2.5. Nutrition Protocol

Infants will be managed according to the NICU nutrition protocol, taking into account international and national guidelines for parenteral and enteral nutrition [25,39,40,41,42,43]. Parenteral nutrition is initiated within the first 2 postnatal hours and early trophic feeding within the first 2 to 4 postnatal days using, preferentially, their mother’s own milk, and when this is insufficient, using donor’s milk. Enteral nutrition is increased as the parenteral nutrition is reduced. Nutritional schedule is as prescribed at the discretion of the attending physician. A powdered multi-component HM fortifier (Aptamil FMS; Danone GmbH, Friedrichsdorf, Germany), containing total energy 3.47 Kcal, protein 0.25 g, and carbohydrates 0.62 g per g of powder, will be started at a dose of 4.4 g/100 mL HM when the HM intake is at least 80 mL/kg/day.

For the fortification method based on measured HM, mothers’ own milk will be analyzed once a week and donor’s milk will be analyzed after the pasteurization. According to the measured HM composition, powdered modular protein (Aptamil Protein Supplement; Danone GmbH, Friedrichsdorf, Germany), containing total energy 3.38 Kcal and protein 0.821 g per g of powder, and medium-chain triglycerides (MCT OIL; Danone, GmbH, Friedrichsdorf, Germany), containing total energy 9.0 Kcal and 1.0 g *per* 1 mL, will be added to fortified HM to reach the target energy and protein daily intakes of total energy 110–135 Kcal/Kg and protein 3.5–4.0 g/Kg [25].

### 2.6. Collected Variables

#### 2.6.1. Retrieved Data

The recorded demographic variables include gestational age, sex, singleton or twin, birth weight, small-, appropriate-, or large-for-gestational age (<3rd percentile, ≥3rd percentile and ≤97th percentile, >97th percentile, respectively) [43], severity index (SNAPPE II) [44], use of prenatal corticosteroids, diagnosis of late sepsis [45], necrotizing enterocolitis (grade ≥ 3) [46], intraperiventricular hemorrhage (grade ≥ 3) [47], multiquistic periventricular leukomalacia [48], and chronic lung disease [49].

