### 2.7. Statistical Analysis

The collected data will be introduced into a Microsoft Excel database (Microsoft Corporation, 2018. Microsoft Excel, available at: https://office.microsoft.com/excel). The Epidemiology and Statistics Office of the Research Center of Centro Hospitalar Universitário Lisboa Central will perform the statistical analysis. To consider the autocorrelation structure due to the longitudinal nature of the study, generalized additive mixed-effect regression models will be used to identify the variables that explain the variability of each continuous outcome variable. Independent variables will be considered throughout the univariable analysis, and all variables with *p* < 0.25 will be selected for the multivariable models. A level of significance of α = 0.05 will be used, although *p*-values greater than 0.05 and lower than 0.1 (weak evidence of difference/association) will eventually be considered. Data will be analyzed using R (R: A Language and Environment for Statistical Computing, R Core Team, R Foundation for Statistical Computing, Vienna, Austria, 2019, http://www.R-project.org.).

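### Exclusions on death, transfer and missed follow-up, with necrotizing enterocolitis and late sepsis open to use as covariates, leave a retained-infants-only view of harm and may bias the growth comparison.

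*Protocol article*

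**What the plan says.** All references are to the protocol article.

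- **Outcomes.** The primary outcome is weight gain velocity (section 2.2). The secondary outcomes are linear growth, head growth and adiposity (section 2.3). No safety or tolerance outcome is named.
- **Recorded variables.** Section 2.6.1 puts "necrotizing enterocolitis (grade ≥ 3) [46" and late sepsis in one list, introduced as demographic, with gestational age, sex and birth weight.
- **Exclusions.** Section 2.4 states that "those transferred to other hospitals, deceased, or unavailable for body composition analysis after discharge will be excluded". The caption of Figure 1 says the drop-out criteria apply to both arms.
- **Models.** Section 2.7 plans models for continuous outcomes only. "Independent variables will be considered throughout the univariable analysis", and those with p < 0.25 go into the multivariable models.
- **Background.** Section 1.3 says "more studies which take into account the osmolality of feeds, feeding tolerance, and risk of necrotizing enterocolitis are needed", with the aim of finding safe maximum concentrations of fortifier and protein supplement.
- **Stated limits.** Section 3.2 mentions neither the selection nor the absence of a safety comparison.

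**The concern.** Two rules act on events that occur after the exposure being compared.

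First, inclusion depends on surviving, not being transferred and attending a visit after discharge. If the fortification method affects any of these, the retained groups are no longer comparable, and complications in infants who died or were transferred are not counted.

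Second, necrotizing enterocolitis and late sepsis are filed with baseline characteristics, and nothing keeps them out of the growth and adiposity models. If one of them lies between fortification and growth, adjusting for it removes that part of the effect from the estimate.

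The conclusions section hopes to identify the best nutrition intervention. A growth advantage estimated under these rules could be reported with only a selected view of its cost.

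**Working it through.** **1. The plan's own figure.** Section 2.4 gives "mean 10.1, SD 3.8 g/Kg/d" for the historical cohort and "mean 12.1, SD 1.6 g/Kg/d" for target fortification, and says "the sample was estimated to detect a difference of 2 g/kg/day in weight gain velocity", "with a significance level of 0.05 and 80% power".

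- Averaged variance: (3.8² + 1.6²)/2 = (14.44 + 2.56)/2 = 8.5, so SD = 2.915.
- n per arm = 2 × 8.5 × (1.960 + 0.842)² / 2² = 33.36, rounded up to 34.

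This reproduces the stated 34 per cohort (68 in total) with a two-sided test. The sample size is not in error. It is set by weight gain alone, and no inflation for exclusions is stated.

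**2. Timing of the events.**

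| Item | When it is known | Role in the text |
|---|---|---|
| Gestational age, sex, birth weight | At birth | Recorded variable |
| Necrotizing enterocolitis, late sepsis | During the stay; may precede or follow the start of fortification | Recorded variable in the same list |
| Death, transfer | During the stay | Exclusion |
| Unavailable for body composition | After discharge | Exclusion |

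Fortification starts only once a set milk intake is reached (section 2.5), so some events will come before it and some after.

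**3. What each analysis needs.** Weight gain velocity uses weights taken in hospital. Body composition is a single measurement after discharge (sections 2.6.2 and 3.2). Missing that visit therefore does not prevent the primary outcome from being calculated, so this exclusion is wider than the primary analysis requires.

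**4. How selection could hide a difference.** The documents give no event rates, so every rate here is an assumption: true enterocolitis risk of 5% in one arm and 10% in the other, 10% of unaffected infants excluded, and a fraction e of affected infants excluded. The risk seen among retained infants is p(1 − e) / [p(1 − e) + (1 − p) × 0.9].

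| e | Risk seen, true 5% | Risk seen, true 10% | Difference (points) |
|---|---|---|---|
| 0.1 (no selection) | 5.0% | 10.0% | 5.0 |
| 0.3 | 3.9% | 8.0% | 4.0 |
| 0.5 | 2.8% | 5.8% | 3.0 |
| 0.7 | 1.7% | 3.6% | 1.8 |

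In counts, excluded cases return to the denominator as well as the numerator. With 34 retained infants and no cases among them, two lost cases give 2/36 = 5.6%, and three give 3/37 = 8.1%.

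**5. What 34 per arm can show even without selection.**

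- Zero cases in 34 leaves a one-sided 95% upper limit of 1 − 0.05^(1/34) = 8.4%.
- Against 0/34, two-sided Fisher p falls below 0.05 only at 6/34 (p = 0.025; 5/34 gives 0.053).
- For an assumed rise from 5% to 10%, approximate power is 11.8% (Fisher 2.8%), and 80% power needs 435 per arm. For 10% to 20%, power is 20.8% (Fisher 12.2%), and 199 per arm are needed.

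These limits come from the sample size, not from the exclusion rule. They mean that any safety report must be descriptive.

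**The case against.** Several stronger readings are tempting, and the documents do not support them.

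- **That the study cannot show harm.** A reader might infer this, but severe enterocolitis and late sepsis are recorded and could be tabulated by arm among retained infants. The flow diagram, which is not shown, may count deaths and transfers. The view of harm is selected, not absent.
- **That section 1.3 commits the study to a safety comparison.** It describes a gap in the literature. The objective in section 1.5 is limited to intakes and quality of growth, and the conclusions then narrow to the same two questions.
- **That an excess of enterocolitis would be adjusted away.** Adjustment changes the growth estimate. It does not remove cases from a count by arm. Section 2.7 also names no candidate variables, so entry of these events is permitted, not certain.
- **That severe cases leave through transfer.** No reasons for transfer are given. Only exclusion on death is explicit.

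It is also fair to say that a morbidity table is a detail an article may leave to a fuller document, and that the exclusions follow the historical cohort's criteria for comparability. Neither point removes the problem. The exclusion and covariate rules are stated in the text, and following them produces the selection and permits the adjustment. Using the same exclusions in both arms does not protect the comparison if fortification affects who is excluded.

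**Conclusion.** The concern holds in a limited form. Following the stated rules restricts any view of harm to retained infants and allows consequences of fortification into the models that estimate its effect on growth and adiposity. The size and direction of any bias in the growth effect cannot be determined from the documents. The drop from 5.0 to between 4.0 and 1.8 points in the visible enterocolitis difference is an illustration on assumed rates. It also requires affected infants to be excluded more often than unaffected ones. The sample size calculation stands, and the article makes no safety claim that it fails to honour. This should be changed because the remedy is specific and modest, but it does not invalidate the design.

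**What to change.** 1. Report necrotizing enterocolitis of grade 3 or above, late sepsis, death and transfer descriptively, by arm and by period, with confidence intervals. Include every eligible infant who started fortified milk, before later exclusions and as far as records and consent allow.
2. State that the study is not powered for safety.
3. Separate in-hospital complications from baseline variables. Do not use enterocolitis or sepsis arising after the start of fortification as candidate covariates in the main comparison of methods. A sensitivity analysis may include them. This requires the date of each event relative to the start of fortification, and the article does not say that these dates are recorded.
4. Apply the exclusion for unavailable body composition to the adiposity analysis only, so that those infants stay in the weight gain analysis.

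The cost is one descriptive table with imprecise estimates, plus some chart retrieval for excluded infants. For 2014–2015 the records of those infants may be incomplete or not held, and any such gap should be stated.

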#### 2.6.2. Measurements

Analysis of HM composition. The HM will be analyzed using the Miris human milk analyzer (Miris AB, Uppsala, Sweden) [50]. To minimize daily variability in breast milk composition, mothers have been asked to add milk collected in 24 h to the same container. The composition is expressed in densities: Kcal/dL of energy and g/dL of fat, raw and true protein, carbohydrates, and ashes.

Assessment of nutrient intake. Daily intakes of energy (Kcal/kg), protein (g/kg), and fat (g/kg), and protein/energy ratio (P/E), provided by administered HM (mL/kg), non-supplemented or supplemented with multi-component HM fortifier and modular protein and fat supplements will be calculated. An Excel program designed to facilitate the calculations of the amount of modular protein and fat supplements to be added to fortified HM was developed and registered ([name], [name], Portuguese Directorate of Intellectual Property Services, IGAC-DSPI, no 480/2020, 26 February 2020).

Assessment of growth and body composition. During the hospital stay, the body weight is routinely measured by the attending nurses, using scales incorporated in incubators or external automatic scales. Weight gain velocity (g/kg/day) is calculated using an exponential model [51]. The same observer ([name]) measures the length and head circumference weekly, according to recommended methods [52,53], to calculate linear and head growth velocities (cm/week). At term, postmenstrual age (around 40 weeks), the fat mass (FM), FFM, %FM, percentage of FFM (%FFM), and FM index (FMI) are assessed using displacement plethysmography (Pea Pod, Cosmed, Italy), as previously described [35]. Both %FM and FMI will be used as indicators of adiposity [35].

